## Materials and Equipment

### Study Design

This will be a multicenter randomized controlled trial (RCT) with five groups that will be realized in primary and specialized care centers from Córdoba (Spain) and its province. Patients will be randomly assigned to receive one of the following interventions: (a) *Brief psychological treatment based on UP*, (b) *Conventional psychological treatment*, (c) *Conventional psychological treatment plus pharmacological treatment*, (d) *Minimum intervention based on basic psychoeducational information, counseling and bibliotherapy*, and (e) *Active comparator treatment as usual (TAU): pharmacological treatment only*. For ethical reasons, in the case of low response to treatment, participants in the *Brief psychological treatment* and *Minimum intervention conditions* will be removed from the trial and will receive the treatment proposed by their GP. Outcome measures will be taken before randomization (baseline assessment), after the intervention (post-treatment assessment) and at 6-month follow-up. The overall study design is summarized in Figure 1. This RCT will be implemented following the SPIRIT guidelines (Chan et al., 2013a,b) and the CONSORT statement (Moher et al., 2010; Schulz et al., 2010).

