Taking into account these results, a generalized medium effect size of 0.6 (Cohen’s *d*) was assumed to detect differences between the interventions and TAU. Due to software to calculate the sample size for analysis using mixed linear models is not available, we established the sample size for analysis of variance using the *f* index trough G^∗^Power. Therefore, we assumed an effect size of 0.3 (*f* index), equivalent to Cohen’s *d* = 0.6. Thus, with a statistical power of 0.80 and an alpha level of 0.05, a total sample of 140 participants will be required (28 subjects in each group). With the objective of controlling the lack of participants throughout intervention and evaluation process, based on previous studies (Farchione et al., 2012; Ito et al., 2016), we assumed an abandonment rate of 15%. Consequently, we require to include 165 participants in our study (33 participants per group).

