#### TAU

The participants included in this experimental condition will receive the TAU prescribed by the GP in PC, based on pharmacotherapy exclusively. The GP will prescribe the TAU to the patient in a regular consultation. This consultation will usually consist of a session between 5 and 7 min in which the GP will evaluate the psychological and physical symptoms of the patients and will prescribe psychotropic drugs. This treatment will be carried out in a maximum period of 8 months.

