## Proposed Analysis

The data will be analyzed following both intention-to-treat (ITT) and per protocol approaches. Firstly, ANOVA or chi-squared will be performed to compare the demographic variables and outcomes measures at baseline. Second, to examine longitudinal changes over time (baseline, posttreatment and follow-up) and between-group differences on these changes we will use linear mixed models, inasmuch as these models are more accurate than repeated-measures ANOVAs (Gueorguieva and Krystal, 2004). In the ITT analysis (all patients randomized are included in the analysis), the incomplete or missing data will be considered using the maximum likelihood estimation method. Additionally, Cohen’s *d* will be calculated to determine the size of between-group effects. Last, we will estimate the Incremental Cost-Effectiveness Ratio (ICER) to compare the relationship between costs and effectiveness of different interventions.

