Due to brief psychological therapies have obtained similar results to conventional psychological therapies (Miller, 2000; Bloom, 2001; Lyons and Low, 2009; Nieuwsma et al., 2012), proving effective in reducing anxious-depressive symptoms (Koutra et al., 2010; Bernhardsdottir et al., 2013; Saravanan et al., 2017), and UP have demonstrated its effectiveness to the treatment of EDs (Barlow et al., 2004; Brown and Barlow, 2009; Farchione et al., 2012), we hope that brief psychological treatment based on UP will be the most efficient treatment and as effective as conventional psychological treatment. However, although there is evidence suggesting that the patient’s improvement, after being treated with brief psychological therapies, remains long after treatment (Hamdan-Mansour et al., 2009; Vázquez et al., 2012), some authors question the maintenance of long-term results (Seekles et al., 2013). Therefore, the results of this study will be added to the evidence of efficacy for brief psychological treatments for EDs right after the treatment and at 6-month follow-up.

By last, we think that “minimum intervention based on basic psychoeducational information, counseling and bibliotherapy” will be more effective than pharmacological treatment for participants included in this study, but will get worst results that different versions of psychological treatment. Due to this kind of interventions are not sufficiently represented in controlled research (Labrador et al., 2000), the results of this work could contribute to the dissemination of minimum psychoeducational interventions to address the treatment of EDs in the PC context.

In last years, new intervention modalities are gaining consensus for the treatment of mental disorders, such as the stepped care approach. This treatment modality consists of apply progressively low and high intensity interventions (Turpin et al., 2008) and is based in two fundamental principles. Firstly, the treatment should produce positive results with the least burden for the patient. Secondly, the results of the patients should be reviewed systematically to decide about the need to move to another level of treatment.

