## Limitations

This study presents several limitations. The first one is related to the design of the study, since the interventions included in the protocol are composed by a different number of sessions. Nevertheless, it is necessary to include interventions with different length to determine whether the treatment effect varies depending on the intensity and duration. Besides, except for the “brief psychological treatment based on UP” group, the number of sessions or weeks of interventions within a certain group could vary from one patient to another. However, we will make sure that each patient is evaluated 6 months after the end of the treatment (follow-up assessment).

As a limitation inherent in this type of studies, considerable dropout rate during the intervention process are expected, as well as a substantial missing data to follow-up. Nevertheless, participants will be animated by phone or email to continue with the treatment or to participate in the follow-up assessment. In addition, the anxious-depressive symptoms could be attenuated by the passage of time.

Other limitations may be related to the recruitment difficulties. Due to the participants must be diagnosed with a DSM-5 disorder and must meet predetermined cutoff points, may be recruitment problems related to the difficulty that participants completely met the eligibility criteria. Besides, patients may refuse to be treated by a different intervention than usual.

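### Low responders leave the trial in the Brief and Minimum arms only, so outcomes after removal are never collected in two of the five arms

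*Protocol article*

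**What the plan says.** All statements are in the protocol article.

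- **Study Design.** For ethical reasons, low responders in the Brief and Minimum conditions "will be removed from the trial and will receive the treatment proposed by their GP". The text gives no threshold or time point for low response, and states no matching rule for the other three arms.
- **Study Design, schedule.** "Outcome measures will be taken before randomization (baseline assessment), after the intervention (post-treatment assessment) and at 6-month follow-up". No assessment during treatment is described.
- **Proposed Analysis.** "The data will be analyzed following both intention-to-treat (ITT) and per protocol approaches". Linear mixed models are fitted to the three time points. In the ITT analysis of all randomized patients, "the incomplete or missing data will be considered using the maximum likelihood estimation method". The per-protocol set is not defined.
- **Sample Size.** 28 evaluable patients per arm, raised to 33 for 15% abandonment. Nothing separate is allowed for removals required by the protocol.
- **Limitations.** Because treatment length varies between patients, "we will make sure that each patient is evaluated 6 months after the end of the treatment (follow-up assessment".
- **Anticipated Results.** The results are to be "added to the evidence of efficacy for brief psychological treatments for EDs right after the treatment and at 6-month follow-up".

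**The concern.** The rule has three explicit features. It depends on outcome, it applies in two of five randomized arms, and it ends participation in the trial and not only in the treatment. An analysis plan cannot recover outcomes that the protocol says will not be collected.

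If the failures of Brief and Minimum disappear while those of the comparators are counted, the two arms look better than they are. That tilt supports the hypotheses that brief is as effective as conventional treatment and that minimum intervention beats drugs. It works against the hypotheses that combined treatment is best and that minimum intervention is worse than conventional treatment. Brief versus Minimum has the rule on both sides. The Conclusion section rests wider use of brief therapy largely on its being as effective as conventional treatment, so the comparison most exposed is also among the most consequential.

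**Working it through.** **The plan's own figures.** For a one-way ANOVA with five groups, f = 0.3 and alpha 0.05, the noncentrality is N × 0.3². Power is 0.792 at N = 135 and 0.809 at N = 140, and 140/0.85 = 164.7, giving 165. Both stated totals reproduce; the sample size is not in dispute.

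**Case 1: removal before a post-treatment score is recorded.**

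Assumptions, none of them in the protocol: higher score is worse; scores are normal with SD 1; correlations are 0.5 for baseline–post, 0.7 for post–follow-up and 0.5 for baseline–follow-up; there is no true arm difference; the worst fraction q on a trigger T is removed. T correlates ρ with the baseline-to-post change, which has SD √(1 + 1 − 2 × 0.5) = 1.

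Let c be the (1 − q) normal quantile, m = φ(c)/(1 − q), and V = 1 − cm − m². Among patients kept, T has mean −m and variance V. Then:

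- mean baseline = +0.5ρm and mean post = −0.5ρm;
- baseline variance = 1 − 0.25ρ²(1 − V);
- baseline–post covariance = 0.5 + 0.25ρ²(1 − V).

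Maximum likelihood regresses post on baseline in the patients kept and averages over all baselines. Its bias towards the affected arm is

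0.75ρm / [1 − 0.25ρ²(1 − V)].

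A per-protocol comparison of change in the patients kept is biased by ρm.

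| Removed q | m | V | ITT post, ρ = 0.5 | ITT post, ρ = 1 | Per-protocol change, ρ = 0.5 |
|---|---|---|---|---|---|
| 5% | 0.109 | 0.810 | 0.04 | 0.09 | 0.05 |
| 15% | 0.274 | 0.641 | 0.11 | 0.23 | 0.14 |
| 30% | 0.497 | 0.493 | 0.19 | 0.43 | 0.25 |
| 40% | 0.644 | 0.422 | 0.25 | 0.56 | 0.32 |

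Worked row, q = 40%: at ρ = 1, 0.75 × 0.644 / (1 − 0.25 × 0.578) = 0.483/0.856 = 0.56; at ρ = 0.5, 0.375 × 0.644 / (1 − 0.0625 × 0.578) = 0.241/0.964 = 0.25.

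At follow-up the same regression gives an ITT bias of about 0.02–0.03/0.06/0.12/0.15 SD at ρ = 0.5.

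**Case 2: removal after a post-treatment score that is kept.** If removal depends only on recorded scores, the mixed model conditions on the scores that caused it. Simulated ITT bias is about 0.00 SD at both later visits for the effect without rescue. An analysis that drops the removed patients at 6 months does not have this protection. Adjusted for baseline, its bias is about 0.03/0.06/0.12/0.15 SD at ρ = 0.5 and 0.05/0.14/0.26/0.34 SD at ρ = 1 under the correlations above. Other correlation sets gave up to 0.36 SD, so these are not upper limits.

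**Numbers left.** If removals come on top of the 15% abandonment, 33 × 0.85 × (1 − q) leaves about 27/24/20/17 patients with later data in each affected arm, against 28 planned.

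**The case against.** Several points on the other side are sound.

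- **Timing.** No assessment is scheduled during treatment, which makes removal after the post-treatment assessment plausible. The flow chart, which might settle it, is not shown. Under that timing the planned ITT mixed model is about unbiased for a no-rescue effect. This stands, and it limits the Case 1 figures to one of two possibilities.
- **Per protocol is undefined.** A Brief patient who completes all eight sessions and gives a post-treatment score may count as per protocol, and a mixed model would use that score. A reader might infer that the 6-month per-protocol result is biased whatever the timing. The document does not support that; it would require that the removed patients, or their post-treatment scores, be dropped.
- **Direction.** A reader might also infer that every comparison must favour Brief and Minimum. That holds for early removal in a no-rescue comparison. Against an estimand that includes later GP care, the sign is open, because rescue could leave removed patients better off than the model predicts, and no rescue effect was modelled.
- **Size.** Removal shares and trigger correlations are assumptions. The 15% abandonment figure is not a removal rate, and removals could overlap with it.

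The statement in Limitations that each patient will be evaluated at 6 months does not answer the point. It replies to variable treatment length and does not mention removed patients. If the sponsor does mean to follow them, the Study Design sentence contradicts that and still needs rewording.

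**Conclusion.** The point holds as a stated, outcome-dependent removal rule in two of five arms, and should be fixed. In either case, outcomes after removal are not collected in those arms, so the 6-month effect of the assigned strategy, including whatever GP care follows, cannot be estimated from observed data.

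Bias in the planned ITT analysis is conditional. It arises if low response is judged before a post-treatment score is recorded, and then ranges from 0.04 to 0.56 SD at post-treatment across the assumed removal shares and trigger strengths, against a planned 0.6 SD. It is about zero, for a no-rescue effect, if a post-treatment score is kept first. Confidence is high on what the rule says, and medium on its consequence because neither the timing nor the removal rate is given.

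**What to change.** Replace removal from the trial with wording such as: low responders stop the allocated intervention, may move to GP-directed care, and remain in the trial with post-treatment and 6-month assessments on the same schedule as everyone else. Record and keep the score at the switch. Base conclusions on ITT using all collected data regardless of switching. Treat per protocol as supportive, and report switches and treatment received by arm.

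The ethical purpose is kept, since low responders still change treatment, and the sample size stays at 165. The cost is protocol and consent wording plus at most two questionnaire assessments per switched patient, about 2 to 13 patients per affected arm (33 × 0.05 to 33 × 0.40).

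There is one real downside. The ITT estimate would include GP care that is available by rule in these two arms only. That care may be the same drugs as in the comparator, whose patients "will receive the TAU prescribed by the GP in PC, based on pharmacotherapy exclusively", so Minimum and TAU may be pulled together. Reporting switches by arm makes this visible, and a no-rescue sensitivity analysis can be run from the same data.

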**FIGURE 1 F1:**
[figure not shown]
Flow chart of the overall study design.

### Instruments and Measures

#### GAD-7 Scale

The GAD-7 scale (Spitzer et al., 2006) is utilized to assess generalized anxiety disorder and other anxiety disorders. In this instrument, participants indicate the presence of anxiety symptoms during the last 2 weeks. The maximum score is 21. The scale has shown high internal consistency (α = 0.89–0.93) (García-Campayo et al., 2010; Zhong et al., 2015).

#### State-Trait Anxiety Inventory (STAI)

The STAI (Spielberger et al., 1983) is a frequently utilized instrument to assess state and trait anxiety. It is composed of 40 items, 20 to assess state anxiety and 20 to assess trait anxiety. A high score indicates the presence of severe anxiety symptoms. This scale has shown excellent internal consistency (α = 0.86–0.95) (Spielberger et al., 1983; Fonseca-Pedrero et al., 2012).

#### Patient Health Questionnaire-9 (PHQ-9)

The PHQ-9 (Kroenke et al., 2001) is a specific screening tool for depression in which participants respond to nine items on depressive symptoms during the last 2 week through a 4-point Likert scale. The intenal consistency of PHQ-9 ranged from 0.86 to 0.89 (Kroenke et al., 2001).

#### Beck Depression Inventory-Second Edition (BDI-II)

The BDI-II (Beck et al., 1996) is a commonly used scale to assess the presence of depressive symptoms in adolescents and adults. The BDI-II is composed of 21 items that cover the diverse symptons of major depressive disorder. Each item is scored on a scale from 0 to 3 (from lowest to highest severity), so the maximum score obtained can be 63 points. The intenal consistency shown by this inventoy has been excellent (α = 0.94) (Arnau et al., 2001).

#### Patient Health Questionnaire-15 (PHQ-15)

The PHQ-15 (Kroenke et al., 2002) is frequently used to measure the presence of somatic symptoms. The Spanish version is composed of 13 and the maximum score for this instrument can be 30 points. The PHQ-15 has shown an acceptable internal consistency (α = 0.78) (Ros Montalbán et al., 2010).

#### Patient Health Questionnaire-Panic Disorder (PHQ-PD)

The PHQ-PD will be use to measure panic disorder symptoms (Spitzer et al., 1999). It is composed of 15 items. We are facing a probable panic disorder when the patient answers affirmatively to the first four items and presents four or more symptoms related to this disorder.

#### Brief Symptom Inventory 18 (BSI-18)

The BSI-18 (Derogatis, 2000) is the shortest version of the Symptom-Checklist 90-R (Derogatis, 1994). It is composed of 18 items and contains three scales (anxiety, depression, and somatization) and a Global Severity Index (GSI). The internal consistency showed by this inventory has been good: GSI α = 0.93, anxiety α = 0.84, depression α = 0.87, and somatization α = 0.82 (Franke et al., 2017).

## Stepwise Procedures

### Sample Size

To establish the sample size, we considered the effect sizes shown by the previous literature. Due to this study pretends to examine the efficacy of several types of interventions, we collected data from previous findings about brief therapies, transdiagnostic treatment, UP, conventional CBT, and combined therapy for the treatment of anxiety disorders and depression. A meta-analytic study examined the effect of various brief psychological therapies in comparison to usual GP care (Cape et al., 2010). The results of the meta-analysis to brief cognitive behavior therapy showed an effect size (Cohen’s *d*) of 1.06 for anxiety, 0.33 for depression and 0.26 for mixed anxiety and depression. In the case of brief counseling, the meta-analysis showed and effect size (Cohen’s *d*) of 0.41 to depression and 0.30 to mixed anxiety and depression. Another meta-analysis (Newby et al., 2015) studied the effect of transdiagnostic psychological treatment for depression and anxiety compared to waitlist, TAU and another psychological treatment, showing a large effect size (Hedges’ *g*) for both depression (*g* = 0.91) and anxiety (*g* = 0.85). Regarding UP, an RCT obtained an effect size (Hedges’ *g*) of 0.56 and 1.11 for anxiety and depression, respectively, using this treatment compared to waitlist (Farchione et al., 2012). Additionally, the findings of a recent meta-analysis about the effect of conventional CBT compared to waitlist, TAU or placebo showed an effect size (Hedges’ *g*) of 0.75 for depression, 0.80 for generalized anxiety disorder, 0.81 for panic disorder and 0.88 for social anxiety disorder (Cuijpers et al., 2016). By last, another meta-analysis examined the efficacy of combined therapies (psychotherapy plus pharmacotherapy) in comparison to pharmacotherapy for the treatment of anxiety disorders and depression (Cuijpers et al., 2014). The findings of this study showed an effect size (Hedges’ *g*) of 0.51 in favor of the combined therapy using CBT compared to pharmacotherapy only.

Taking into account these results, a generalized medium effect size of 0.6 (Cohen’s *d*) was assumed to detect differences between the interventions and TAU. Due to software to calculate the sample size for analysis using mixed linear models is not available, we established the sample size for analysis of variance using the *f* index trough G^∗^Power. Therefore, we assumed an effect size of 0.3 (*f* index), equivalent to Cohen’s *d* = 0.6. Thus, with a statistical power of 0.80 and an alpha level of 0.05, a total sample of 140 participants will be required (28 subjects in each group). With the objective of controlling the lack of participants throughout intervention and evaluation process, based on previous studies (Farchione et al., 2012; Ito et al., 2016), we assumed an abandonment rate of 15%. Consequently, we require to include 165 participants in our study (33 participants per group).

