### The Present Study

The aim of this work is to examine the efficacy of several types of interventions, in therapeutic and cost-effectiveness terms, for the treatment of patients with EDs. The different interventions are the following: brief psychological treatment based on UP; conventional psychological treatment; conventional psychological treatment plus pharmacological treatment; minimum intervention based on basic psychoeducational information, counseling and bibliotherapy; and pharmacological treatment.

We hypothesize that “conventional psychological treatment plus pharmacological treatment” will be the most effective treatment, but “brief psychological treatment based on UP” will be the most efficient treatment (cost-effectiveness). Besides, we expect that psychological treatment (brief and conventional) will be more effective than pharmacological treatment, but less effective than “conventional psychological treatment plus pharmacological treatment,” and that “brief psychological treatment” will be as effective as “conventional psychological treatment” but more efficient than this one. Finally, we think that “minimum intervention based on basic psychoeducational information, counseling, and bibliotherapy” will be more effective than pharmacological treatment but will get worst results that different versions of psychological treatment.

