## Anticipated Results

This research protocol pretends to highlight the importance of adapting treatments to real contexts of application, and their adjustment to brief formats of limited time that maximize the cost-benefit of implemented care, as other authors suggest (Kazdin, 2008; Moriana and Martínez, 2011), besides contributing to the dissemination of psychological treatments in primary and specialized care.

The principal objective of this work is to examine the effectiveness and the efficiency of the brief psychological treatment in a sample of patients with EDs, compared to other four treatments: conventional psychological treatment, conventional psychological treatment plus pharmacological treatment, minimum intervention based on basic psychoeducational information, and pharmacological treatment. Although we think that psychological treatment (brief and conventional) will be more effective than pharmacological treatment, as suggested by previous results with patients with EDs (Heuzenroeder et al., 2004; Watts et al., 2015), we expect that “conventional psychological treatment plus pharmacological treatment” will be the most effective treatment. This findings will be compliant with other studies that indicate that the combined treatment is superior in efficacy to CBT and pharmacotherapy alone in both anxiety disorders (Furukawa et al., 2007; Van Apeldoorn et al., 2008) and depression (Keller et al., 2000; Pampallona et al., 2004).

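### The stated 0.80 power is that of a five-group omnibus test at f = 0.3; one intervention against TAU at d = 0.6 has about 0.60, and the hypothesis that combined treatment is most effective is not powered

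*Protocol article*

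**What the plan says.** The Sample Size section reviews published effects and then says that "a generalized medium effect size of 0.6 (Cohen’s *d*) was assumed to detect differences between the interventions and TAU". Because the authors found no software for mixed models, "we established the sample size for analysis of variance using the *f* index", and "we assumed an effect size of 0.3 (*f* index), equivalent to Cohen’s *d* = 0.6". The result, for power 0.80 at alpha 0.05, is that "a total sample of 140 participants will be required (28 subjects in each group"), raised to 165 (33 per group) for 15% dropout.

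The hypotheses are mostly comparisons between named arms. The Present Study opens with "We hypothesize that “conventional psychological treatment plus pharmacological treatment” will be the most effective treatment". It then places brief and conventional psychological treatment below combined treatment but above drug treatment, and minimum intervention between the psychological treatments and drug treatment. Anticipated Results repeats that "we expect that “conventional psychological treatment plus pharmacological treatment” will be the most effective treatment", but gives the principal objective as brief treatment compared with the other four. Under Proposed Analysis, for "between-group differences on these changes we will use linear mixed models", with Cohen's d for between-group effects.

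**The concern.** A reader of the Sample Size section will take it that the trial has 80% power to show a difference of d = 0.6 between an intervention and TAU. An omnibus F test asks only whether the five means are all equal. Its power is not the power of any single comparison, and f = d/2 is the conversion for two equal groups, not five.

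The gap is wider for the first-stated hypothesis. For combined treatment to be the most effective, it must exceed each of the other four arms, including the two psychological ones. The only planning effect is against TAU; no size is given for combined treatment against another active arm. A non-significant difference there would be likely even if the hypothesis were true, and it should not be read against a background of 80% power.

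**Working it through.** **Inputs from the Sample Size section:** five equal groups, f = 0.3, d = 0.6 against TAU, alpha 0.05, power 0.80, 28 per group (140), 15% dropout, 165 (33 per group). The type of analysis of variance and the sidedness of alpha are not stated; I take a one-way omnibus F test and two-sided pairwise tests with no multiplicity adjustment.

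**1. The plan's own figure.** Noncentral F with λ = f²N on 4 and N − 5 df. At N = 140, λ = 0.09 × 140 = 12.6 and power is 0.809. At 27 per group it is 0.792, so 28 is the smallest equal group size that reaches 0.80. Dropout: 140/0.85 = 164.7, so 165. Both figures reproduce.

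**2. All four interventions 0.6 above TAU.** With one fifth of patients on TAU, f = 0.6 × √(0.2 × 0.8) = 0.24, not 0.30. Then λ = 0.0576 × 140 = 8.06 and power is 0.59 (0.68 at N = 165). Reaching 0.80 would need 43 per group, 215 in all, before dropout.

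**3. One intervention against TAU at d = 0.6.** Two-sample noncentral t with noncentrality d√(n/2) = 0.6 × √14 = 2.245 on 54 df: power 0.60 (0.67 with 33 per arm).

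**4. Combined treatment against one other active arm.** The document gives no effect, so d is an assumption:

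| assumed d | power, 28 per arm | power, 33 per arm |
|---|---|---|
| 0.1 | 0.07 | 0.07 |
| 0.2 | 0.11 | 0.13 |
| 0.3 | 0.20 | 0.22 |
| 0.4 | 0.31 | 0.36 |

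With 28 per arm, 80% power on one such contrast needs d of about 0.76, more than the whole effect assumed over TAU.

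**5. Combined treatment superior to all four arms.** Simulation with pooled variance, 28 per arm; the means are assumptions that follow the hypothesised order:

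| TAU / minimum / brief / conventional / combined | power to beat all four |
|---|---|
| 0 / 0.17 / 0.34 / 0.34 / 0.51 | 2% |
| 0 / 0.2 / 0.4 / 0.4 / 0.6 | 3% |
| 0 / 0.3 / 0.6 / 0.6 / 0.8 | 3% |
| 0 / 0.294 / 0.588 / 0.588 / 0.883 | 8% |
| 0 / 0.294 / 0.4 / 0.4 / 0.883 | 23% |

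The first row puts combined treatment 0.51 above TAU, the only effect cited for combined treatment against drugs alone. The fourth has equal steps scaled to f = 0.3 exactly. Power reaches 44% only if combined treatment lies 1.2 above TAU and 0.6 above both psychological arms.

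**6. Baseline adjustment.** Steps 1 to 5 use one timepoint, as the plan's own calculation appears to. If the baseline–outcome correlation is ρ, adjustment turns d into d/√(1 − ρ²). For d = 0.6 against TAU with 28 per arm, ρ = 0.5 gives 0.6/√0.75 = 0.69 and power 0.72; ρ = 0.7 gives 0.6/√0.51 = 0.84 and power 0.87. The equal-step figure for beating all four arms rises from 8% to 11% and 18%. The plan states no ρ and does not use one.

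**The case against.** The plan limits its effect size to interventions against TAU, so it can be said never to have claimed 80% for comparisons among active arms. That is fair, and it is why this point is about stating the scope. It does not rescue the figure for the comparison that the plan does name: d = 0.6 against TAU has about 0.60 on the plan's own basis.

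The mixed model uses baseline and includes every randomised patient, so real power may be higher. This stands. With a strong baseline correlation the TAU comparison could pass 0.80, though that is not the stated basis, and the claim that combined treatment beats every arm stays far from it.

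Three stronger readings are tempting, and the document does not support them:

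- A reader might infer that power for the combined-treatment hypothesis is 8%. That is one point in a range set by assumed means that the document does not give.
- A reader might infer that planning on one common effect makes the hypothesis false by construction. But the word generalized can mean an average over varied literature effects. The equal-step means average (0.294 + 0.588 + 0.588 + 0.883)/4 = 0.588 over TAU and give f = 0.300, so 0.6 and 0.3 are compatible with the hypothesised order.
- A reader might infer that arms will be ranked by observed mean after a significant omnibus test. No section says so, and the detailed decision rules may stand in an analysis plan that is not shown.

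**Conclusion.** The point holds as a mismatch between the stated power and the hypotheses. The 0.80 is omnibus power at f = 0.3. It is neither the power of one intervention against TAU at d = 0.6 (about 0.60) nor that of the omnibus test under a uniform effect of 0.6 (about 0.59). The first-stated hypothesis, that combined treatment is most effective, is not powered: no effect is assumed for it, and any single contrast with an active arm has about 0.07 to 0.31 for assumed d of 0.1 to 0.4.

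The results against TAU follow from the plan's own inputs. Those among active arms rest on assumed differences and should be read as a range. All assume 28 evaluable patients per arm, two-sided alpha 0.05, no multiplicity adjustment and no baseline adjustment. I call the combined-treatment hypothesis first-stated and not principal, because Anticipated Results names brief treatment against the other four as the principal objective.

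**What to change.** In Sample Size, say that 0.80 is the power of the five-group omnibus test at f = 0.3 only. Give the pairwise power against TAU at d = 0.6 (about 0.60 with 28 per arm, before any baseline adjustment). Say that comparisons among the active arms are not powered, with the range for d = 0.1 to 0.4 marked as an assumption.

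In The Present Study, Proposed Analysis and Anticipated Results, commit to reporting combined minus conventional and combined minus brief as differences with 95% confidence intervals. Call combined treatment the most effective only if it is superior to each other arm, not on the omnibus p-value.

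Optionally, add one planned 1-df contrast in the hypothesised order (weights −1.6, −0.6, 0.4, 0.4, 1.4 from TAU to combined). If the equal-step order is true, λ is again 12.6, now on 1 and 135 df, and power is 0.94 against 0.81 for the omnibus test. With four equal interventions the two tests are level (0.60 against 0.59). The contrast supports a trend across the order and does not establish the superiority of any one arm, so it does not replace the changes above.

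The cost is wording, with no extra patients or assessments. The downside is a less favourable stated power.
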